#### Design of the health economic evaluation

The objective of the health economic analysis is to estimate differences in total societal costs between the two approaches in relation to the difference in quality-adjusted life-years gained (incremental cost-utility ratios) over the 2-year follow-up. This analysis will be followed by analysing its dependence on personal characteristics. The estimation includes two steps: (a) quantify all resource use related to illness and treatment, as well as the HRQoL in physical terms and (b) evaluate uses of resources in monetary terms and calculate a utility measure between minus and plus one from the HRQoL instrument.^44^ A ratio will also be created which is the incremental cost (the cost difference between intervention and usual care groups) divided by the incremental effect (corresponding difference in utility).

Resource use will include data from the regional patient register VEGA (held by Region Västra Götaland), which covers all care reimbursed by the region, including hospital, outpatient and primary care conducted within the region but also care received in other regions. Information on prescribed medication and related costs will be obtained from the National Board of Health and Welfare. In addition, data on lost productivity for the patient due to sickness absence (ie, absence from work which can be attributed to sickness) will be retrieved from the MiDAS database (Social Insurance Agency) and self-report in patient questionnaires (since the first 14 days of each sick leave is not covered by official statistics). This information will be used to estimate indirect costs (sometimes called productivity costs) using the human capital approach, which entails multiplying the net days on sick leave by the mean wage and associated social security contributions. The difference in costs and utilities will be compared (assuming that there will be no difference in length of life between the two groups) and cost-utility ratios will be estimated. Several issues are involved in valuing healthcare in monetary terms related to the basic economic–theoretical concept of ‘opportunity cost’, true societal valuations and marginal costs. We will follow the state-of-the-art practice by making alternative estimates of costs and present the results as sensitivity analyses.^45^ Such analyses will be a test of the robustness of the results. HRQoL (measured by EQ-5D) will be collected repeatedly in the patient questionnaires. As a sensitivity analysis, we will use both a general population value set from the UK,^43^ as there is no such value set validated for Sweden, and a Swedish experience-based value set^38^ for the translation of EQ-5D results into utilities. Sensitivity analyses will also address length of follow-up. Missing data from the questionnaires will be considered as missing at random and thus handled using a multiple imputation strategy.

Dependence of personal characteristics (eg, education and income, collected from the LISA database at Statistics Sweden and through patient questionnaires) will be tested. The distribution of costs will also be analysed by major stakeholders, that is county councils/regions, market sectors (productivity loss) and individuals/families/friends to facilitate the more limited approaches to economic evaluation. For details, see figure 1.

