## Introduction

Chronic heart failure (CHF) and chronic obstructive pulmonary disease (COPD), two long-term conditions common in older populations, are associated with high rehospitalisation rates and high mortality.^1 2^ In addition, both conditions severely affect activities of daily living because of frequent symptoms that limit health-related quality of life (HRQoL), compelling patients to be dependent on others.^3^ Patients with CHF and/or COPD frequently require hospital care and the severity of their symptoms often leads to repeated visits to hospital, outpatient or primary care.^1–3^ Although pharmacological therapy has improved outcomes markedly over the past 10–15 years, management programmes are still needed to optimise care.^4^ There are benefits of pulmonary rehabilitation (eg, reduction in readmission and mortality), including exercise training, education and self-management interventions that specifically target behaviour change for patients with COPD.^5^ A consistent recommendation in the treatment of CHF is management programmes designed to improve outcomes through structured follow-ups that increase patients’ self-care skills and other key issues (eg, symptoms and disease trajectory).^2^ Being affected by a chronic disease with a high symptom burden is a major challenge to living a full life. Healthcare professionals (HCPs), such as registered nurses, occupational therapist and physiotherapist, in conjunction with well-developed technology, can serve to enable successful self-management for individuals with severe long-term illnesses.^6^

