#### Primary end point

The primary end point will be the composite score of change in general self-efficacy and rehospitalisation or death 6 months after randomisation.

A patient will be classified as deteriorated if:

General self-efficacy has decreased by ≥5 units.Patient has been hospitalised for unscheduled reasons due to COPD/CHF.Patient has died due to all causes.

A patient is classified as improved if:

General self-efficacy has increased by ≥5 units.Patient has not been hospitalised due to COPD/CHF.Patient has not died.

Those who have neither deteriorated nor improved are considered unchanged.

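### The cost-utility analysis assumes equal length of life in the two arms, so any survival difference is left out of a QALY comparison in which deaths are observed

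*Protocol article*

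**What the plan says.** All of the following is in the Protocol article.

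- **Objective** (Design of the health economic evaluation): the societal cost difference is to be set against "the difference in quality-adjusted life-years gained (incremental cost-utility ratios) over the 2-year follow-up".
- **Ratio** (same section): the cost difference is "divided by the incremental effect (corresponding difference in utility").
- **Survival** (same section): costs and utilities are compared "assuming that there will be no difference in length of life between the two groups".
- **Utilities** (same section): "HRQoL (measured by EQ-5D) will be collected repeatedly in the patient questionnaires". Questionnaires are mailed at inclusion and at 3, 6, 12 and 24 months (Sources and collection of data).
- **Missing data** (same section): "Missing data from the questionnaires will be considered as missing at random and thus handled using a multiple imputation strategy".
- **Sensitivity analyses** (same section): alternative cost estimates, two EQ-5D value sets, and length of follow-up.
- **Deaths**: the Introduction calls the two conditions "associated with high rehospitalisation rates and high mortality". The primary end point classes a patient as deteriorated if "Patient has died due to all causes". Sources and collection of data says that death is followed for every participant.

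**The concern.** A QALY difference has two parts: how long patients live and how well they live. The objective asks for both, and the survival assumption sets the first to zero before any data are seen. The trial has no need of such an assumption, because it follows deaths in everyone and counts them in its primary end point.

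Two things are at stake. First, if mortality differs between the arms, the effect side of the ratio omits the life-years gained or lost, while costs taken from registers reflect the survival that actually occurred. Second, even if true mortality is equal, the observed numbers of deaths will differ by chance. Assuming equality leaves that uncertainty out of the result. None of the listed sensitivity analyses would show a reader how much depends on it.

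**Working it through.** The plan gives no figure for mortality, utility or QALYs, so there is none to reproduce on this point. All mortality and utility values below are assumptions.

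**Inputs.** Horizon 2 years (health economic section). Assumed: utility u of 0.6 to 0.8; deaths spread evenly over the 2 years, so 1 year is lost per death on average; utility 0 after death. The 2-year mortality is m_C in the control arm and m_I in the intervention arm, and d is the utility gain among the living.

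**Step 1: the part left out.** Mean QALYs per arm are utility × (2 − m). With d = 0 the true difference is u × (m_C − m_I); under equal length of life it is 0. The omitted QALYs per patient are therefore (mortality difference) × 1 year × u:

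| Mortality difference | u = 0.6 | u = 0.7 | u = 0.8 |
|---|---|---|---|
| 1 point | 0.006 | 0.007 | 0.008 |
| 2 points | 0.012 | 0.014 | 0.016 |
| 5 points | 0.030 | 0.035 | 0.040 |
| 6 points | 0.036 | 0.042 | 0.048 |

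As a yardstick, a utility gain of 0.03 held for 2 years is 0.03 × 2 = 0.06 QALY.

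**Step 2: with a utility gain as well.** The true difference is (2 − m_I)(u + d) − (2 − m_C)u = d(2 − m_I) + u(m_C − m_I). Under equal length of life it is 2d, which is 0.060 for d = 0.03.

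- 5% in both arms: 0.03 × 1.95 = 0.0585. The error is 0.0015, close to nil.
- 10% control, 5% intervention, u = 0.7: 0.0585 + 0.035 = 0.0935. The gain is understated.
- 10% control, 15% intervention, u = 0.7: 0.03 × 1.85 − 0.035 = 0.0205. The gain is overstated about threefold (0.060 / 0.0205 = 2.9).
- 6% control, 12% intervention, u = 0.8: 0.03 × 1.88 − 0.048 = 0.0084. The gain is small but still positive.

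**Step 3: when the sign would change.** Let x be the excess mortality in the intervention arm, with m_C = 6%, u = 0.8 and d = 0.03. The true difference is zero when 0.03 × (1.94 − x) = 0.8x, so x = 0.0582 / 0.83 = 0.070. A reversal needs about 7 points of excess mortality, or a smaller utility gain.

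**Step 4: uncertainty left out.** The Project timeline reports 224 patients; I assume 112 per arm and 10% mortality. The standard error of the mortality difference is √(2 × 0.10 × 0.90 / 112) = 0.040. At 1 year lost per death and u = 0.7 that is 0.040 × 0.7 = 0.028 QALY, about half of the 0.06 yardstick.

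**The case against.** The strongest reply is that the assumption may do little harm. Participants come from primary care, and severe disease with expected survival under 12 months is excluded. The high mortality in the Introduction describes the diseases, not this selected sample. A 1 to 2 point difference would move the result by no more than 0.016 QALY. A 6 point gap such as 12% against 6% is only about 13 against 7 deaths at 110 per arm. The planned analyses by length of follow-up would include a shorter horizon with fewer deaths. All of this stands as a limit on size. It does not justify the assumption, since the exclusion covers 12 months of a 24-month horizon, and varying the follow-up does not test equal survival.

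A reader might infer more than the documents support in four ways:

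- **That deceased patients will be given survivors' utilities.** The imputation rule makes no exception for death, but it does not say that a questionnaire never due from a deceased patient counts as missing. A fuller health economic plan could set utility to 0 at death.
- **That the ratio divides by a utility difference rather than by QALYs, which would double a 2-year ratio.** The same section states the objective in QALYs, and the later phrase can be read as shorthand for that effect.
- **That the sign of the effect will be wrong.** For mortality gaps of up to 6 points and a 0.03 utility gain, it is not (Steps 2 and 3).
- **That an arm with more deaths will look cheaper.** The documents give no cost data, including costs near death, so the direction on the cost side is unknown.

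**Conclusion.** The point holds for the survival assumption. It is a stated rule rather than a detail left to another document, it conflicts with the QALY objective in the same section, and it replaces information that the trial collects. Under the assumptions above, the omission ranges from near nil with equal mortality, through 0.006 to 0.016 QALY per patient for a 1 to 2 point difference, to 0.030 to 0.048 for 5 to 6 points. The direction depends on which arm has more deaths. The imputation and denominator wording needs clarifying but is not shown to be wrong.

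This is a should-fix for a secondary, health economic end point. The primary analysis and the sample size are unaffected.

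**What to change.** 1. Remove the equal-survival assumption from the main cost-utility analysis.
2. Compute each patient's QALYs as the area under the EQ-5D utility curve over 0, 3, 6, 12 and 24 months, with utility 0 from the recorded date of death.
3. State that the denominator of the ratio is the between-arm difference in mean QALYs.
4. State that multiple imputation under missing at random applies only to questionnaires missing while the patient is alive.
5. If wanted, keep equal survival as a labelled sensitivity analysis.

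The cost is a change of wording in the analysis plan and a somewhat more variable QALY difference, because deaths now contribute to it. No new measurements are needed, since death is already followed for all participants; the sponsor should confirm that dates of death are held for the full 24 months. The change should be made before the cost-utility analysis is run.

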#### Exclusion criteria

No device with internet access, that is, no computer, smartphone or tablet.Severe impairment that prevents persons from using e-health support.No registered address.Any severe disease with an expected survival of <12 months.Cognitive impairment.Ongoing documented diagnosis of alcohol/drug abuse.Other diseases that can interfere with follow-up (eg, severe depression and other severe mental illnesses).Participating in another conflicting study.

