#### Sources and collection of data

Data will be collected using self-report instruments, interviews, study documentation, medical records and administrative registers. Questionnaires will be mailed (together with a prepaid return envelope) to the participants at study inclusion and 3, 6, 12 and 24 months after randomisation. Paper questionnaires were chosen since not all of the instruments are validated for online use. Follow-ups and adverse events (ie, admission to hospital or death) will be controlled for all participants. Baseline data (including demographics, characteristics and medical history) will be collected from the patients’ medical records. For details, see figure 1.

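### The cost-utility analysis assumes equal length of life in both arms, so a mortality difference within the 2-year horizon would be left out of the QALY comparison

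*Protocol article*

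**What the plan says.** Under Design of the health economic evaluation, the protocol article states that its objective concerns "quality-adjusted life-years gained (incremental cost-utility ratios) over the 2-year follow-up". It then describes a ratio whose denominator is a difference in utility. Later in that section, costs and utilities are to be compared "assuming that there will be no difference in length of life between the two groups".

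Four other statements bear on this:

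- The Introduction says that the two conditions "are associated with high rehospitalisation rates and high mortality".
- Under Sources and collection of data, "adverse events (ie, admission to hospital or death) will be controlled for all participants". Questionnaires go out at inclusion and at 3, 6, 12 and 24 months.
- All-cause death counts as deterioration in the 6-month primary end point ("Patient has died due to all causes").
- The survival-related exclusion is "Any severe disease with an expected survival of <12 months", which is half the economic horizon.

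On missing data, the economic section says: "Missing data from the questionnaires will be considered as missing at random and thus handled using a multiple imputation strategy". Its sensitivity analyses cover alternative cost estimates, two EQ-5D value sets and length of follow-up.

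**The concern.** A QALY is time alive weighted by utility. Fixing the between-arm difference in length of life at zero removes one of its two components, in an analysis whose stated effect is QALYs over a period in which patients will die. Survival is an outcome of the randomised comparison, and the trial records deaths. The plan puts an assumption in place of that information, and none of the listed sensitivity analyses clearly relaxes it.

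The error has a known direction on the effect side. If one arm has more deaths, its lost life-years are not charged to it, so its QALY result is too favourable. This works both ways: an intervention that lengthened life would get no credit for doing so. The incremental cost-utility ratio is a listed secondary end point, and the Discussion ties implementation to cost-effectiveness, so a distorted QALY difference would matter to readers.

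**Working it through.** The plan states no QALY, utility or mortality figure, so there is none of its own to reproduce here. The check asks how large a difference the equal-life rule can hide.

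**Inputs from the document.** Horizon of 2 years; 224 patients included (Project timeline), taken as 112 per arm.

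**Assumed inputs.** Constant hazard; two-year mortality *d* of 15% and 20%; mean utility while alive of 0.65 (range 0.5 to 0.8); between-patient utility SD of 0.25, independent of survival.

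**1. Mean life-years within 2 years.** With *h* = −ln(1 − *d*)/2, the restricted mean is *d*/*h*.

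- *d* = 0.15: *h* = 0.08126, mean = 0.15/0.08126 = 1.846 years
- *d* = 0.20: *h* = 0.11157, mean = 0.20/0.11157 = 1.793 years
- Difference: 0.053 life-years. Five points of mortality is 0.05 × 112 = 5.6 deaths in an arm.

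**2. In QALYs, with equal utility while alive.**

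| Utility | QALY difference with deaths counted | Under equal length of life |
|---|---|---|
| 0.50 | 0.027 | 0 |
| 0.65 | 0.035 | 0 |
| 0.80 | 0.043 | 0 |

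A cruder model gives the same size. If deaths are spread evenly over the 2 years, mean life-years are 2 − *d*, so 10% versus 15% differs by 0.05 years, or 0.030 to 0.040 QALY at utility 0.6 to 0.8.

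**3. Combined with a utility gain.** Let utility be 0.67 with the intervention and 0.65 with usual care. Under equal length of life the gain is always 2 × 0.02 = 0.040.

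- Mortality 20% (intervention) versus 15%: 0.67 × 1.7926 − 0.65 × 1.8459 = 0.001
- Mortality 15% (intervention) versus 20%: 0.67 × 1.8459 − 0.65 × 1.7926 = 0.072
- Mortality 15% in both: 0.02 × 1.8459 = 0.037

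The rule can therefore overstate or understate the gain. It is nearly harmless when mortality is equal.

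**4. Chance imbalance.** With true mortality of 15% in both arms, the SD of life-years within 2 years is 0.429. The standard error of the difference is 0.429 × √(2/112) = 0.0574 life-years. In QALYs the 95% range is ±1.96 × 0.0574 × 0.65 = ±0.073.

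**5. Standard error of the QALY difference.**

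- Equal length of life: 2 × 0.25 × √(2/112) = 0.0668
- Deaths counted: the mean square of life-years is 3.592, so the variance is (0.65² + 0.25²) × 3.592 − (0.65 × 1.8459)² = 0.302, the SD is 0.550, and the standard error is 0.550 × √(2/112) = 0.0735
- Understatement: 1 − 0.0668/0.0735 = 9%

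**The case against.** The case for leaving the plan alone has four parts.

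- **It is a secondary analysis.** All-cause death already counts in the primary end point, so deaths are not hidden from the main conclusion. This stands, and it limits the severity.
- **The assumption has some basis.** Recruitment is from primary care, patients with very short expected survival are excluded, and the E-health section reports that earlier telephone-based person-centred support did not raise the risk of clinical events. This explains why no survival effect was expected. It does not justify setting aside deaths that are recorded.
- **The magnitudes are hypothetical.** True: every rate and utility above is assumed, and the 0.001 versus 0.040 example pairs a utility gain with a mortality gap that nearly cancels it. The direction on the QALY side does not depend on those values.
- **The clause may refer only to survival after the trial.** The text does not support this. The sentence governs the 2-year comparison, and no extrapolation is described.

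A reader might also infer three stronger points that the documents do not support:

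- **That costs fall in the arm with more deaths, so that arm gains on both sides of the ratio.** The article does not say how costs behave around death. Register costs of delivered care would end there, but care before death can be expensive, so the net direction is uncertain. Costs that end at death are in any case real costs and not a bias.
- **That every death to 24 months is certain to be observed.** Deaths are tracked for all participants, but no time window is given. The 24-month window is an inference from the follow-up schedule.
- **That patients who die will be given imputed living utilities.** The missing-data sentence permits this if read literally. It does not say that a questionnaire never due because of death counts as missing, and an article may leave that detail to the full plan.

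**Conclusion.** The equal-life assumption is wrong as written and should be fixed. It is an explicit rule, so the allowance for detail left to a fuller plan does not cover it, and it conflicts with the section's own QALY objective.

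Bias in the estimate requires a mortality difference, whether real or by chance. Given one, the QALY difference favours the arm with more deaths. A 5-point gap (15% versus 20%) is worth about 0.03 to 0.04 QALY per patient at utility 0.5 to 0.8, and the plan scores it as zero. Even with equal underlying mortality, the uncertainty of the QALY difference is somewhat understated, by about 9% under the stated inputs. These sizes rest on assumed mortality, utility and SD. The point does not touch the primary end point or the sample size, and no claim is made about the direction on costs.

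**What to change.** Remove the equal-length-of-life assumption from the main cost-utility analysis. Compute each patient's QALYs as the area under the utility curve over 24 months, with utility 0 from the date of death. State that multiple imputation applies only to questionnaires that fell due while the patient was alive. Keep the equal-survival version, if wanted, as a labelled sensitivity analysis.

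The cost is a sentence or two in the economic plan and a little programming. No new type of data is needed, provided that dates of death are ascertained to 24 months in both arms, which the plan should confirm. The confidence interval for the QALY difference becomes slightly wider.

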#### Design of the process evaluation

A mixed-method approach will be applied as it is suitable to deal with the complexity of the intervention by combining the strength of qualitative and quantitative methodologies.^46 47^ Quantitative and qualitative strands will be integrated by adding findings from different subprojects to understand intervention outcomes and by combining methodologies within subprojects. The primary objective of the process evaluation is to widen and deepen the understanding of intervention mechanisms of impact. Two key questions will guide the evaluation:

How do people diagnosed with CHF and/or COPD experience that the intervention and their internal and external capabilities influenced intervention outcomes?How are HCPs, other invited partners and people diagnosed with CHF and/or COPD interacting the intervention in their everyday life?

##### Exploring experiences of the intervention and internal and external capabilities in relation to programme outcome

A grounded theory approach^48^ will guide data collection and analysis. The method is suitable to study processes and actions and to deepen the understanding of contextual influences. Data will be collected postintervention (6-month follow-up) through individual face-to-face interviews or through phone according to the participant’s preferences. Purposeful selection of participants will be used. Initial sampling criteria are set up to reach heterogeneity regarding age, gender, diagnosis, educational level and degree of use of the intervention. Of note, 10–15 interviews are predicted to be needed but inclusion will continue until saturation is reached. A question guide with one opening question and question areas concerning features of intervention content and design and internal/external prerequisites will be used. Interviews will be audio recorded and transcribed verbatim. Initial and focused coding will be used during analysis that is conducted by an experienced qualitative researcher. In the initial coding, each line will be coded close to the data. Later segments of data will be synthesised and explained using a conceptual code (focused coding). Codes within and between interviews will be compared and sorted into categories. Memos will be used to systematically compare codes and to document analytical thoughts.^48^

